## Abstract

**Background:**

There has been substantial increase in use of androgen deprivation therapy as adjuvant management of prostate cancer. However, this leads to a range of musculoskeletal toxicities including reduced bone mass and increased skeletal fractures compounded with rapid metabolic alterations, including increased body fat, reduced lean mass, insulin resistance and negative lipoprotein profile, increased incidence of cardiovascular and metabolic morbidity, greater distress and reduced quality of life. Numerous research studies have demonstrated certain exercise prescriptions to be effective at preventing or even reversing these treatment toxicities. However, all interventions to date have been of rehabilitative intent being implemented after a minimum of 3 months since initiation of androgen deprivation, by which time considerable physical and psychological health problems have manifested. The pressing question is whether it is more efficacious to commence exercise therapy at the same time as initiating androgen deprivation, so treatment induced adverse effects can be immediately attenuated or indeed prevented.

**Methods/design:**

We are proposing a multi-site randomized controlled trial with partial crossover to examine the effects of timing of exercise implementation (immediate or delayed) on preserving long-term skeletal health, reversing short- and long-term metabolic and cardiovascular risk factors, and supporting mental health in men receiving androgen deprivation therapy. 124 men who are about to initiate androgen deprivation for prostate cancer will be randomized to immediate or delayed groups. Immediate will commence a 6-month exercise program within 7–10 days of their first dose. Delayed will receive usual care for 6 months and then commence the exercise program for 6 months (partial cross-over). Immediate will be free to adopt the lifestyle of their choosing following the initial 6-month intervention. Measurements for primary and secondary endpoints will take place at baseline, 6 months and 12 months.

**Discussion:**

This project is unique as it explores a fundamental question of when exercise implementation will be of most benefit and addresses both physical and psychological consequences of androgen deprivation initiation. The final outcome may be adjunct treatment which will reduce if not prevent the toxicities of androgen deprivation, ultimately resulting in reduced morbidity and mortality for men with prostate cancer.

**Trial registration:**

ACTRN12612000097842

## Background

There has been a substantial increase in the use of temporary androgen deprivation therapy (ADT) as an adjuvant to radical radiation and surgical therapies for management of prostate cancer
[1,2] with substantial periods of ADT now routinely applied to improve outcomes at 5, 10 and 15 years post diagnosis
[2-4]. More than 2,000 men in Australia
[5] and more than 80,000 in the USA
[6] commence on-going ADT for prostate cancer each year. However, ADT leads to a range of well-established musculoskeletal toxicities including reduced bone mass and increased skeletal fractures
[7,8] compounded with rapid metabolic alterations including increased body fat, loss of lean mass, insulin resistance and negative lipoprotein profile
[9-15]. Recent work, including our own current Australian cohort, suggests an increased incidence of cardiovascular and metabolic morbidity associated with temporary ADT
[16-20] and we have also reported significantly increased distress
[21] and reduced quality of life (QOL)
[22,23]. Our team has shown that even a 9-month exposure to ADT leads to significant reductions in bone mass across different clinical sites concurrent with severe loss of lean mass and increased trunk and whole body fat mass, all surrogate indicators of osteoporosis/skeletal fractures and cardiovascular/metabolic complications
[15]. Currently, there is no established treatment to reverse bone loss and the array of metabolic adverse effects associated with severe hypogonadism from temporary ADT. Preliminary clinical trials by our team
[24-26] and others
[27,28] have suggested high efficacy of exercise for these patients but evidence is limited to only a few studies with men on long-term androgen deprivation
[24,27-29]. We have shown that a combined program of resistance and aerobic exercise leads to a number of significant and clinically meaningful benefits including reversal of muscle loss in men receiving ADT for an average of approximately 14 months
[24]. A critical but as yet unanswered research question is to determine whether it is more efficacious to commence exercise therapy at the onset of androgen deprivation so treatment induced adverse effects can immediately be attenuated or even completely prevented. This has not been addressed in any exercise trials to date and has the potential to prevent much of the ADT toxicities from the outset rather than try to rehabilitate the patient from the effects of long-term ADT later. A recent report
[30] showed that physical function and quality of life are compromised within 3 months of commencing ADT suggesting that up-front exercise interventions are needed to counteract these losses, as well as the marked reductions in bone density and bone strength. Importantly, it appears the initial beneficial effects of resistance and aerobic exercise programs are similar for neuromuscular and physical function regardless of whether patients are on acute (3–6 months) or chronic (>6 months) ADT
[31]. Such preliminary evidence supports the hypothesis that exercise might be best initiated when ADT commences, to enhance physical function, retain structure and improve the patient’s acceptance of hormone therapy. This is an important finding as it suggests that exercise may still benefit men during acute ADT, but no research has trialled this from time zero; that is initiation of ADT. This is a considerable gap in our understanding of the management of prostate cancer and ADT.

Having successfully completed several pilot studies, a randomised controlled trial (RCT) and ongoing RCTs in prostate cancer
[24-26,31-34], this trial will drill down to the specifics of exercise as medicine to improve skeletal health, physical function, quality of life and mental health implemented immediately when patients initiate ADT. We propose a RCT with partial crossover to examine the effects of the timing of exercise implementation. We will evaluate the following hypotheses:

1) It is more efficacious to commence exercise therapy at the onset rather than after six months of ADT; and

2) ADT side effects, in particular the substantial initial bone loss, can be prevented by a 6-month exercise program concurrently undertaken at the onset of ADT.

The primary endpoint will be spine and hip aBMD determined by DXA. Secondary endpoints will include: 1) volumetric BMD (vBMD) and micro-architecture at the tibia, 2) body composition (lean mass and fat mass/abdominal obesity), 3) blood pathology (glucose metabolism, lipid profile, prostate specific antigen (PSA), testosterone, bone formation and resorption markers), 4) physical function, muscle strength and balance, 5) physical activity level and motivation, and 6) health-related quality of life and psychological distress.

The ultimate outcome will be guidelines for the prescription of exercise for the prevention of ADT toxicities, primarily those related to long-term skeletal health and physical function. This project is unique as it explores a fundamental question of when exercise implementation will be of most benefit to men undertaking ADT. The final outcome may be an adjunct treatment which will prevent major toxicities of ADT, ultimately resulting in reduced morbidity and mortality for men with prostate cancer.

## Methods/design

We are proposing a single-blinded (investigators and testing personnel blinded to group allocation) RCT with partial crossover to examine the effects of the timing of exercise implementation. An immediate exercise group (IE) will undertake the exercise program for 6 months. After 6 months, the delayed exercise group (DE) will be crossed to receive the same intervention program (Table
1).

**Table 1 T1:** Summary of the Intervention Arms

	**0**	**6**	**12**
**Immediate Exercise (n=62)**	Exercise Intervention		No formal intervention
**Delayed Exercise (n=62)**	Usual Care		Exercise Intervention

### Recruitment

Subjects will be recruited by invitation of their specialist (radiation oncologist/urologist) as previously reported in completed and ongoing trials
[24,26,32]. Those entering the study will undertake a series of familiarisation sessions and baseline measurements prior to randomisation (Figure
1).

**Figure 1 F1:**
[figure not shown]
CONSORT Diagram.

### Randomisation and stratification

Patients will be randomly allocated in a ratio of 1:1 to the two treatment arms for IE and DE groups, subject to maintaining approximate balance regarding stratification for age (<=70 yr>) and smoking status (yes/no). A research methods consultant will be responsible for this randomisation and confirming the groups are balanced on these parameters. The chief investigators, exercise physiologists, psychologists and other researchers conducting the study measures will be blinded to a given participant’s group allocation. The exercise intervention will be provided by exercise physiologists not in the research team or performing the tests (single blinded).

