### Calculation of sample size

Data from our 36-week study
[15] in prostate cancer survivors initiating ADT indicates that the standard deviation (SD) for change in our primary outcome of BMD equates to approximately 4.5% and 3.3%, for the hip and lumbar spine, respectively. With ADT, the annual loss is reported to be 2-8% at the spine and 1.8-6.5% at the hip
[49,50] and based on our 36-week data, we obtained an initial loss of 1.5% and 3.9% for the hip and lumbar spine, respectively. Therefore, we anticipate losses of approximately 1.5% and 3.5% at the clinically relevant fracture sites of the hip and spine. We anticipate a difference between the immediate and delayed exercise groups of approximately 2.5% at the hip and 4.5% at the lumbar spine, which would be clinically significant and substantially reduce the risk for fracture. A priori, 51 subjects per group will be required to achieve 80% power at an alpha level of 0.05 (two-tailed), and to demonstrate a difference between groups at each bone site at the end of the 6-month intervention. Previous experience in our exercise trials indicates an attrition rate of up to 20% over the course of the study period. Therefore, to adequately ensure that we have sufficient subject numbers at the end of the intervention, 124 subjects will be randomised in a ratio of 1:1 to the immediate and delayed exercise groups, respectively. A sample size of 124 will also provide us with sufficient power to detect differences in our secondary outcomes which all have larger effect sizes based on our previous research.

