### Statistical analysis

Data will be analysed using SPSS statistical software package and an intention-to-treat approach will be applied. Analyses will include standard descriptive statistics, Student’s *t* tests, correlation and regression, and two-way (group x time) repeated measures ANOVA (or ANCOVA as appropriate) to examine differences between groups over time. All tests will be two-tailed and an alpha level of 0.05 will be applied as the criterion for statistical significance.

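### The between-group test is left as repeated measures ANOVA, or ANCOVA when judged appropriate, so adjustment for baseline and for the balancing factors is permitted but not fixed

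*Protocol article*

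**What the plan says.** Under Randomisation and stratification, the protocol article allocates patients 1:1 "subject to maintaining approximate balance regarding stratification for age (<=70 yr>) and smoking status (yes/no"). A research methods consultant is to confirm that the arms are balanced on these two factors. Baseline BMD is not one of them. Under Recruitment, baseline measurements come before randomisation. Under Measurements, the primary and secondary endpoints are taken at baseline, 6 and 12 months.

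Under Statistical analysis, the listed methods are descriptive statistics, t tests, correlation and regression, and "two-way (group x time) repeated measures ANOVA (or ANCOVA as appropriate) to examine differences between groups over time". No covariate is named, and nothing says what makes ANCOVA appropriate.

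Under Calculation of sample size, the trial is sized on change in BMD at 6 months: "51 subjects per group will be required to achieve 80% power at an alpha level of 0.05 (two-tailed"), with SDs of change in "BMD equates to approximately 4.5% and 3.3%, for the hip and lumbar spine, respectively" and "a difference between the immediate and delayed exercise groups of approximately 2.5% at the hip and 4.5% at the lumbar spine".

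**The concern.** The design uses age and smoking to balance the arms and has a pre-randomisation value of every continuous endpoint, but the stated analysis commits to none of these as covariates. Two things are at stake.

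- **Precision.** If age and smoking predict bone change, leaving them out keeps their variance in the error term, and the standard errors are larger than they need to be. An unadjusted change comparison is also less efficient than one adjusted for baseline. The hip calculation has little room for this.
- **Choice of test.** With no stated rule, the analyst can choose between an unadjusted and an adjusted test of the primary endpoint with both results in view. The nominal two-sided 5% level then no longer describes the procedure.

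**Working it through.** **1. The plan's own figure.** Inputs from Calculation of sample size: alpha 0.05 two-sided, power 80%, SD of change 4.5% (hip) and 3.3% (spine), difference 2.5% (hip) and 4.5% (spine).

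n per group = 2 × (1.960 + 0.842)² × (SD/difference)²

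- Hip: 2 × 7.849 × (4.5/2.5)² = 50.9, so 51. This is the stated figure.
- Spine: 2 × 7.849 × (3.3/4.5)² = 8.4, so 9.

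The hip drives the sample size, and no covariate adjustment was assumed. By the t test, 51 per group gives 79.3% power at the hip. The plan allows "an attrition rate of up to 20% over the course of the study period"; at 20%, 62 per arm leaves 62 × 0.8 = 49.6 and 78.2% power.

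**2. Gain from adjusting for baseline at 6 months.** Let s be the SD at each visit (assumed equal) and rho the baseline-to-6-month correlation.

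- Change score: variance 2s²(1 − rho)
- ANCOVA: residual variance s²(1 − rho²)
- Ratio: (1 + rho)/2

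The article does not give rho, so a range is shown for the hip:

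| rho | Variance ratio | n per group for 80% power | Power at 51 per group (t test) | Power at 49.6 per group (t test) |
|---|---|---|---|---|
| change score | 1.000 | 51 | 79.3% | 78.2% |
| 0.95 | 0.975 | 50 | 80.3% | 79.2% |
| 0.9 | 0.950 | 49 | 81.3% | 80.2% |
| 0.8 | 0.900 | 46 | 83.4% | 82.3% |
| 0.7 | 0.850 | 44 | 85.4% | 84.4% |
| 0.5 | 0.750 | 39 | 89.4% | 88.6% |

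**3. Which rows apply to BMD.** From 4.5² = 2s²(1 − rho), rho = 1 − 4.5²/(2s²), with s in percent of the mean. The article does not give s. If it lies between 10 and 18 (assumption), rho is 0.90 at s = 10, 0.93 at 12, 0.955 at 15 and 0.97 at 18. The saving is then 0 to 2 subjects per arm, or about 0.6 to 2 points of power. Rho of 0.5 to 0.7 would be more typical of a noisier outcome. For such outcomes the variance falls by 15 to 25%, again under assumed rho.

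**4. Gain from age and smoking.** If they explain a share R² of the variance of hip BMD change, the variance is multiplied by (1 − R²). R² is not given. At R² of 0.01, 0.05 and 0.10, the n per group is 51, 49 and 46. At R² = 0 there is no gain.

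**5. Cost of the open choice.** Simulation under no treatment effect: 50 per arm, normal data, 40,000 runs for each rho. If the smaller p-value of the change-score test and ANCOVA is always reported, the type I error is about 5.8 to 5.9% at rho 0.90 to 0.95, 6.5% at 0.7 and 7.2% at 0.5. These are worst cases.

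**The case against.** The strongest reply is that a journal article commonly leaves the covariate list to a statistical analysis plan, which is not shown here. That stands: the missing list alone is no finding. What remains is that the article itself states an open choice between an unadjusted and an adjusted test for the comparison between groups.

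Several stronger readings are tempting and are not supported:

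- **That the plan ignores baseline and the strata.** Baseline is a time level in the repeated measures ANOVA, the sample size already works on change, and ANCOVA and regression are both permitted. No covariate is excluded.
- **That baseline BMD was used to balance the arms.** Only age and smoking were.
- **That the planned group-by-time test is the change-score test.** This holds for two time points. With baseline, 6 and 12 months the interaction has 2 degrees of freedom, so the ratio in the working applies only to a separate baseline-to-6-month contrast.
- **That the primary analysis loses much power.** For BMD the likely loss is small, and the spine needs only 9 per group. Nothing in the article shows that the age cut or smoking predicts 6-month bone change. If they do, leaving them out is conservative and not invalid.
- **That ANCOVA will be chosen on seeing baseline imbalance.** The article does not say what triggers it. The wording leaves the timing open and is no evidence of intent.

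**Conclusion.** The point holds in a limited form. The primary comparison may be run without baseline, age stratum or smoking as covariates, and no rule fixes the choice before the data are seen. The cost in precision is probably 0 to 2 subjects per arm at the hip. That estimate rests on equal variances at the two visits and an assumed baseline SD of 10 to 18% of the mean. For secondary outcomes with rho of 0.5 to 0.7, the variance reduction on offer is 15 to 25%. Any gain from the strata depends on how well they predict change, which is unknown. The possible inflation of the type I error is modest, from 5% to about 6% for BMD-like correlations in the worst case. The analysis as written is not invalid and the sample size need not change. This is an improvement available at almost no cost, from data the trial already collects.

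**What to change.** In Statistical analysis, replace the ANOVA-or-ANCOVA phrase as the between-group test with one model named in advance: 6-month value on arm, with baseline value, age stratum (cut at 70 years) and smoking status as covariates. An equivalent arm-by-visit model with the same covariates will also do, if the 6-month contrast is declared primary. Use the same form for the continuous secondary outcomes. Deleting only the words that permit ANCOVA would not be enough, because it would leave the unadjusted ANOVA as the sole named test.

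The cost is a change of wording, made before outcome data are examined, and about three degrees of freedom out of about 100. No new data are needed and the total stays at 124. Adjustment for region (Western Australia or New South Wales) is optional, since region is not a stated balancing factor.

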### Subjects

One hundred and twenty-four men (62 subjects per arm) beginning treatment for prostate cancer involving ADT with no regular exercise (undertaking structured aerobic or resistance training two or more times per week) within the past 3 months will be recruited by invitation of their attending specialist in the Perth, Western Australia, and the Central Coast region of New South Wales. All participants will be able to walk 400-m and will require physician consent. Exclusion criteria will include prior exposure to ADT (e.g. those re-initiating ADT from intermittent programs), existing hypogonadism, established metastatic bone disease, established osteoporosis, those taking medications known to affect bone metabolism (e.g. bisphosphonates), acute illness or any musculoskeletal, cardiovascular or neurological disorder that could inhibit or put them at risk from exercising. The protocol has been approved (ID: 7869 [name]) by the University Human Research Ethics Committee and all subjects will provide written informed consent.

### Measurements

All measurements for primary and secondary endpoints will take place at baseline, 6 and 12 months. Additional blood measures, scans and questionnaires will also be undertaken at 3 months to track changes over time during the initial 6 months for bone formation and resorption markers. Body composition measures for muscle and fat mass will also be performed at 3-month intervals to track the trajectory of change in these outcomes.

### Calcium and vitamin D

All participants will receive standard daily supplementation with calcium (1,000 mg/d) and vitamin D_3_ (800 IU/d).

### Primary study endpoints

#### Areal BMD

BMD (g/cm^2^) of the hip (total hip) and lumbar spine (L_2-4_) as well as whole body bone mineral content (BMC, g) will be assessed by DXA (Hologic Discovery A, Waltham, MA). The Instant Vertebral Assessment (IVA) and Quantitative Morphometry (QM) program will be used to determine the presence or absence of vertebral fractures prior to initiation of the study.

### Secondary study endpoints

#### Volumetric BMD and bone architecture

Three dimensional pQCT (XCT3000, Stratec, Pforzheim, Germany) will be used to measure volumetric BMD and micro-architecture at the tibia. This technique provides additional data on trabecular and cortical density and geometry with actual prediction of fracture thresholds. Methods for analysis will be as previously described
[35].

#### Body composition

In addition to BMD, regional and whole body lean mass (including appendicular skeletal muscle mass) and fat mass will be derived from the whole body DXA scan. Measurement of trunk adiposity is an important indicator of chronic disease risk, and will be assessed from trunk fat mass obtained from the whole body scan and the ratios of trunk fat to limb fat, and trunk fat to total fat. Images from the pQCT scans will also be analysed for muscle density and cross-sectional area for the lower limbs.

#### Blood markers

Testosterone, prostate specific antigen (PSA), insulin, glucose, haemoglobin A1c (HbA1c), C-reactive protein (CRP), bone formation [alkaline phosphatase, Pro collagen Type 1 N-Terminal Pro peptide (PINP)] and resorption [C-terminal telopeptide of type I collagen (CTX)] markers, vitamin D and lipid profile levels will be measured commercially by an accredited Australian National Association of Testing Authorities (NATA) laboratory (Pathwest Diagnostics, Perth, Western Australia)
[24].

#### Blood pressure and arterial stiffness

A validated oscillometric device (HEM-705CP, Omron Corporation, Japan) will be used to record brachial BP at the dominant arm in triplicate. Central (ascending aortic) BP and indices of arterial stiffness will be determined using a SphygmoCor system (AtCor Medical, Sydney, Australia). Radial artery pressure waveforms will be captured at the right arm by applanation tonometry using a high fidelity micromanometer (SPC-301, Millar Instruments, Houston, Texas, USA). A generalised transfer function is applied to the radial artery waveform in order to obtain the pressure waveform at the ascending aorta. This method has been validated against invasive techniques for determination of central BP and the augmentation index (AIx) is a marker of systemic arterial stiffness.

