### Exercise intervention

The intervention program will comprise resistance, aerobic and impact-loading exercises undertaken 3 times per week in an exercise clinic. The frequency of resistance and aerobic exercises will alternate weekly so two aerobic/impact loading and one resistance/impact loading sessions are performed in the first week and two resistance/impact loading and one aerobic/impact loading are performed in the subsequent week. Resistance training sessions will take approximately 60 minutes (this includes the warm-up and cool-down periods) and will be conducted in the Exercise Clinics at Edith Cowan University (ECU) in Perth and seven other partner sites in Western Australia: Perth; Mandurah; and Bunbury. We also have another site at the University of Newcastle where we have identical equipment and procedures. The programme will include exercises such as leg press, leg extension, leg curl, chest press, seated row, lat pulldown and bicep curl that target the major upper and lower body muscle groups, which we have used in a number of previous studies

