[24,26,37,47] including men on ADT. To ensure the progressive nature of the training program, subjects will be encouraged to work past the specific repetition maximums (RMs) prescribed. The resistance will be increased by 5-10% increment for the next set/training session if the subject is able to perform more repetitions than the RMs specified during a set. Intensity will be manipulated from 6-12-RM (e.g. the maximal weight that can be lifted 6 to 12 times) using 1–4 sets per exercise. The aerobic component will include 25–40 minutes of cardiovascular exercise using various modes such as walking or jogging on a treadmill, cycling or rowing a stationary ergometer, or exercising on a cross training machine. Target intensity will be 60-85% estimated maximum heart (220–age) with individual heart rate watches (Polar Electra Oy, Finland) provided for each participant. In addition to the clinic training, participants will be encouraged to undertake twice weekly home-based training incorporating aerobic activity (e.g. walking, cycling) and a modified version of the impact-loading regimen (only including hopping, leaping and drop jumping) for the duration of the study. The impact-loading regimen will be performed a minimum of 3 times per week for the duration of the trial, in combination with the resistance and aerobic exercise. For the first 10 weeks, 2 rotations will be performed of skipping (30 sec), bounding over soft hurdles (13–16 cm), and drop jumping (10–15 cm). In the second 10-week period, hopping on one leg (10 times) will be added, leaping (10 times) will replace skipping, and 4 rotations of bounding (19–25 cm), drop jumping (20–25 cm), hopping, and leaping will be performed for the remainder of the programme. These activities result in substantial peak ground reaction forces ranging from 3.4 to 5.2 times body weight providing excellent stimulus to bone yet proven safe and accepted by older people
[48].

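### Cuff pressure and radial waveform are assigned to different arms in left-handed men, and the heart-rate handling of augmentation index is left open (low severity)

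*Protocol article*

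**What the plan says.** The protocol article, under Secondary study endpoints, section Blood pressure and arterial stiffness, fixes two measurement sites. For the cuff, an oscillometric device "will be used to record brachial BP at the dominant arm in triplicate". For tonometry, "Radial artery pressure waveforms will be captured at the right arm by applanation tonometry". A transfer function then converts the radial waveform to an aortic one.

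On outputs, the section says "Central (ascending aortic) BP and indices of arterial stiffness will be determined using a SphygmoCor system". The only index it names is augmentation index (AIx): "the augmentation index (AIx) is a marker of systemic arterial stiffness". Heart rate is not mentioned there.

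Under Exercise intervention, "The intervention program will comprise resistance, aerobic and impact-loading exercises undertaken 3 times per week in an exercise clinic". For the aerobic part, "The aerobic component will include 25–40 minutes of cardiovascular exercise using various modes", and "Target intensity will be 60-85% estimated maximum heart". According to the abstract and Table 1, the delayed group has usual care for the first 6 months and then starts the programme.

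Statistical analysis is one general paragraph for all endpoints: repeated measures ANOVA, or ANCOVA where suitable, with no covariate named for any outcome.

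**The concern.** There are two separate issues in one short section.

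The first is written procedure. A tonometry waveform has to be scaled to a cuff pressure, and the brachial reading is the only cuff pressure described. Where the two sites fall on different arms, any pressure difference between the arms passes into the derived central pressure. The plan creates that error in left-handed men for no stated reason.

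The second is something left open. AIx depends on heart rate: at a slower rate ejection lasts longer, the reflected wave adds more to the systolic peak, and the index rises with no change in the artery. In many trials this is only noise. Here one group trains aerobically for 6 months while the other does not, so a training effect on resting heart rate would follow the randomised contrast and push raw AIx against exercise. Randomisation does not remove a difference that arises after it.

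At stake is the reading of central pressure and stiffness as cardiovascular risk measures, an area that the abstract names among the trial's aims.

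**Working it through.** **Part 1: measurement arm.** Inputs: the two site rules above, 124 men (62 per group, Table 1), and an assumed 8-12% left-handed; the article gives no figure for handedness.

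- Right-handed man: dominant arm = right arm, so cuff and waveform come from one arm.
- Left-handed man: dominant arm = left, waveform arm = right, so they come from opposite arms.
- Men affected: 124 × 0.08 = 9.9 and 124 × 0.12 = 14.9, so about 10 to 15. Per group: 62 × 0.08 = 5.0 to 62 × 0.12 = 7.4.

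Let p be the left-handed proportion and d(t) a left-handed man's inter-arm difference at visit t. The error in his change score is about d(6) − d(0). If d is stable, this is close to zero. If d varies between visits with mean change zero, it adds about p × Var[d(6) − d(0)] to the variance of change. Since p is expected to be equal in the two groups, the between-group contrast gains noise, not expected bias. On its usual definition AIx is a ratio of pressures within one waveform, so linear rescaling leaves it unchanged. This part therefore concerns central pressure.

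**Part 2: AIx and heart rate.** The article gives no AIx effect, SD or heart-rate change, so there is no figure of its own to reproduce. Its sample size supplies the number per group for an illustration. For the hip, n = 2 × (1.960 + 0.842)² × (4.5/2.5)² = 50.9, hence the stated 51.

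Bias in raw AIx = slope (points per bpm) × between-group fall in resting rate (bpm). Both inputs are assumptions.

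| Slope | 0 bpm | 2 bpm | 5 bpm | 8 bpm |
|---|---|---|---|---|
| 0.3 | 0 | 0.6 | 1.5 | 2.4 |
| 0.4 | 0 | 0.8 | 2.0 | 3.2 |
| 0.5 | 0 | 1.0 | 2.5 | 4.0 |

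For scale, the difference detectable with 80% power at 51 per group is 2.802 × SD × √(2/51) = 0.555 × SD. That is 2.8, 3.9 and 5.5 points for an assumed SD of change of 5, 7 and 10.

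For an assumed SD of 7 and a true benefit of −4 points:

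| Bias | Expected raw difference | Power to show benefit |
|---|---|---|
| 0 | −4.0 | 0.82 |
| 0.6 | −3.4 | 0.69 |
| 2 | −2.0 | 0.30 |
| 4 | 0 | essentially none (0.025) |

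For a true benefit of −3, a bias of 4 would give +1. The range thus runs from no effect to masking or a reversed sign, and the article does not show where in that range the trial lies.

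**The case against.** A reader might infer that the plan has chosen to analyse raw AIx, and that its stiffness comparison is therefore biased against exercise. The documents do not support that. The section speaks of indices in the plural and states neither a raw nor a heart-rate-adjusted form. The analysis paragraph leaves covariates open. A condensed article commonly leaves such detail to a full protocol or analysis plan, and neither is shown. Nor does the article say that AIx varies with heart rate or that resting rate will fall; it mentions heart rate only as a training target. Clinic aerobic sessions alternate between two and one per week, an average of (2 + 1)/2 = 1.5, with further home activity only encouraged, so a fall near zero is possible. The 12-month direction is also undetermined, because the immediate group may do as it wishes after month 6. All of this stands. What remains is a request to name the AIx form, not a demonstrated error.

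It can also be objected that adjustment has its own cost. If training lowers heart rate, concurrent heart rate is affected by treatment, and using it as a covariate estimates a different, partly mediated contrast. That stands too. Conversely, a covariate measured only at baseline would not capture a change in heart rate during treatment.

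On the arm mismatch, the article does not say which cuff reading scales the waveform, a stable inter-arm difference largely cancels in change scores, and both groups are affected alike. These points limit the size but do not remove the inconsistency. The two site rules are stated text, and cancellation holds only as far as the difference is stable and the same procedure is followed at each visit.

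**Conclusion.** The point holds at low severity. The arm mismatch is a flaw in stated procedure. It affects about 10-15 of 124 men if 8-12% are left-handed and if the described cuff reading is the one used for scaling. It adds mainly noise to central pressure, in both groups alike.

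The heart-rate handling of AIx is unspecified. If raw AIx were analysed, the 6-month contrast could be biased against exercise by 0 to 4 points, on an assumed fall of 0-8 bpm at 0.3-0.5 points per bpm. Masking or reversal is possible at the upper end and absent at the lower end.

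Neither part touches the primary endpoint of spine and hip bone density. Arterial stiffness has its own heading among the secondary endpoints but is not in the six-item list in the Background, and no power statement is specific to it.

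**What to change.** - Take brachial pressure and the radial waveform at the same arm for every man at every visit. The right arm would do, since tonometry is already placed there. This is one line in the measurement procedure.
- Name the AIx outcome in advance: AIx normalised to a fixed heart rate (for example 75 bpm), reported together with unadjusted AIx and resting heart rate by group and visit. Normalisation changes the question asked, so the reader needs all three to separate an arterial change from a rate change.
- Do not rely on concurrent heart rate as a covariate alone. If such a model is fitted, label it supportive and say that it conditions on a post-randomisation variable.

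The cost is small. Heart rate is contained in the recorded waveform, so no extra measurement is needed, and the sample size and primary analysis do not change.
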